### Phases of the trial

The trial will have the following three phases: Refer to Figure 2.

1) Inception & piloting phase. The main purpose of the two-year phase is to develop, pilot and refine the care delivery guidelines/ materials and trial design/ protocols before embarking upon the trial registration.

– The piloting experiences and results will enable the research team to:

– Assess the feasibility and acceptability, and then accordingly modifythe process for health facility selection (i.e. facility assessment, providers’ and communal consent for the trial etc.) and management support (logistic supplement, reporting, monitoring etc.)

– Assess the feasibility and acceptability, and then accordingly modifythe case management guidelines i.e. diagnosis, treatment, record keeping, follow-up etc.

– Assess the feasibility and robustness of the research protocols, then accordingly modify, the protocols for case inclusion/ exclusion, recruitment rate, and periodic assessment (research related).

– Revisit the assumed proportion of diabetics, dyslipidemic and smoker patients among adult hypertensive patients in local context.

– Revisit the assumptions about sample size calculation to meet the power of the study such as mean change (± standard deviation) in systolic blood pressure, glycaemic and cholesterol control, and tobacco cessation between intervention and control arms.

– Assess and modify, if needed, the proposed statistical methods to analyze the trial data.

– The qualitative interviews with providers (± patients) for assessing the feasibility during the trial piloting will also be adapted subsequently for the trial assessment. In short the trial piloting will inform the decision to implement the trial to get optimal results and valid evidence.

2) Trial Implementation phase

– In the first 03 months of the trial implementation phase, the following arrangements will be made before start registering cases in the trial.

– Refine the case management guidelines/ materials Assess and shortlist the health facilities for possible inclusion in the trial. Randomization :The ASD central trial unit, under the supervision of Trial Steering Committee, will then randomize the facilities into two trial arms. Randomization preformed will be simple randomization. Each participating facility (cluster) will be given a unique ID which the investigators will be blinded to.12 different sheets of paper will be taken and the unique ID of each cluster will be written on the paper, which will be folded and sealed into an envelop.12 such sealed envelopes will be made. Then by a simple procedure, 6 sealed envelopes will be selected by hand picking them randomly from the pile of 12 sealed envelopes.6 will be hand picked for the intervention arm and 6 sealed envelopes for the control arm. The Steering committee will consist of a director, two people from ASD and two people from in-country (PMRC) and international partners (WHO).

– At least two doctors and two paramedics from each participating facility will be trained. The intervention facility staff will be trained on enhanced case management guidelines and materials including recording reporting and enhanced follow-up and referral, whereas the control facility staff will be trained only to register and report, use patient education brochure, and access HbA1c and cholesterol testing for trial patients.

– In the next 06 months of the trial implementation phase, the patients will be registered and enrolled in the trial, as per agreed protocols. During the period the baseline hypertension measurement will be validated by an external expert examination, kept blind to the trial arm as well as any previous measurements.

– The case management enhancement in the intervention arm will include: case management desk-guide for patient care, flip chart and brochure for patient education, mobile link for late patient retrieval, referral for advanced care (if needed), regular monitoring and support.

– Once the required number of trial patients is enrolled in the trial, the subsequent patients will receive HTN-CVD and associated care from the respective facility (as per prevailing case management protocols i.e. either intervention or control) but their results will not be included in the trial evaluation.

– The research team will closely monitor the inclusion and exclusion of trial patients, mainly to identify and respond to any deviation from the research protocols and/or case management processes.

– In the next 15 months of the trial implementation phase, the registered trial patients will be followed-up to measure the outcomes.

– All patients will pay for the case management services, as per facility protocols. However, the measurement of hypertension, HbA1c, serum cholesterol and carbon mono oxide in exhaled air will be paid from the project sources (as these measurements are being made solely for the trial evaluation). The referral to district headquarter hospital, as required, for specialist consultation (e.g. cardiology, ophthalmic examination, renal assessment, drug side effect) will be managed as per agreed guidelines for intervention arm and as per current routine in the control arm. The specialist facility will be encouraged to refer back patients to the respective referring facility, after providing the requested specialist care.

– The case management record on each patient will be maintained in the chronic disease register (to be developed and introduced through the trial inputs). The chronic disease register at each facility will provide the data for detailed analysis on case management experiences in the two trial arms.

– The modalities for periodically monitoring the participating facilities (including reviewing records and collecting reports) will be developed during the initial development phase (see section 12 below). The research team will ensure that each participating facility is monitored as per guidelines agreed for the respective facility (i.e. intervention and control).

– The research team will also supplement the logistic inputs at the participating facilities. This includes maintenance of BP apparatus, glucometer and supplies, print materials etc. at the participating facilities.

3) Intervention Evaluation and Research Take-up phase

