#### Control arm

The control for comparison is the current care practices (for hypertension and associated conditions) at the private health care facilities. The only addition will be a) enhanced screening and diagnosis, b) introduction of HTN-CVD register for collecting core data set on patients attending these control facilities. In ‘current practice’, each practitioner manages HTN-CVD cases, as per his/her self-determined regimen and without reference to any specific guidelines and/or tools.

The health staff at a facility will offer the same care package to all its HTN-CVD cases, regardless of their social strata and other preferences. This will reduce the chances of intra-cluster contamination as well as strengthen and simplify the implementation of prospective evaluation. All trial patients will be asked to arrange their prescribed drugs, so that the trial reflects the real life practice in private health care delivery system.

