#### Recruiting participants

The eligible for inclusion patients will be informed and offered to participate (see inclusion/ exclusion criteria above). The patient is recruited only if he/she consents to participate.

Once recruited, each patient in the:

– control arm will be offered standardized diagnosis and care as per current practice, whereas intervention arm will be offered an enhanced HTN-CVD care including standardized diagnosis, prescription, follow-up, and monitoring.

– intervention arm will also be educated on life style modifications recommended for the individual, whereas control arm patients will receive information brochure.

– both arms will be asked to arrange the prescribed medicine through their own sources. However, access to baseline BP, HbA1c, cholesterol examination will be facilitated, for both arms, through trial resources.

Both arms will be requested to adhere to the treatment protocols.

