### Addressing bias, error and limitations

Comparing the socio-demographic and health services profiles of the private facilities does not indicate any significant difference that can potentially lead to differences in care seeking behavior and/or quality of service. The proposed cluster randomization is expected to address the potential selection bias across the two trial arms.

The process of equal screening and diagnosing training in both arms will lead to similar disease intensity patients being recruited in both arms. Although similar training of health professionals in both arms in regards to better screening this will eliminate selection bias, it will lead to a inability to measure ‘case detection rate’ due to better screening.

The lack of masking (blinding) could introduce bias through two routes i.e. “incorrect measurement” and “leakage” from one group to another. There was a possibility of incorrect measurement of “blood pressure outcomes” by the facility doctor, who is aware of the intervention allocation. This possibility of measurement bias will be reduced through an unrelated external BP monitoring doctor who is unaware of the intervention allocation. Contamination across clusters is prevented by keeping a minimum distance between clusters.

The proposed randomization does not allow asking and responding to individual patient preferences. So the trial will not answer the question what would happen if health services are able to offer intervention according to individually tailored patient needs/ convenience. Further work will be needed to test the approaches sensitive to individual preferences, in the local programme setting.

The proposed method of randomization, ie concealed simple randomization has its own limitations. This method does not address the balance of baseline covariates. An alternative approach could have been addresses the need to control and balance the influence of covariates by using stratified randomization. This method can be used to achieve balance among groups in terms of baseline characteristics (covariates) of health facilities based on socio demographics of catchment population they feed into, size of health facility, patient load etc. Different strata /blocks of health facilities may have been made and then simple randomization done in each strata to achieve a balance of covarites. This could have minimized the biased that simple randomization does not address.

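### The list of control-arm staff training leaves out screening and diagnosis, contradicting the equal training on which the protocol rests its selection-bias claim

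*Protocol article*

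**What the plan says.** All references are to the Protocol article.

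- **Phases of the trial, trial implementation phase, control staff:** "control facility staff will be trained only to register and report, use patient education brochure, and access HbA1c and cholesterol testing for trial patients".
- **Same place, intervention staff:** "intervention facility staff will be trained on enhanced case management guidelines and materials including recording reporting and enhanced follow-up and referral".
- **Control arm**, on what is added to current practice: "The only addition will be a) enhanced screening and diagnosis, b) introduction of HTN-CVD register".
- **Recruiting participants:** "control arm will be offered standardized diagnosis and care as per current practice".
- **Addressing bias, error and limitations:** "The process of equal screening and diagnosing training in both arms will lead to similar disease intensity patients being recruited in both arms". The next sentence draws the inference that "similar training of health professionals in both arms in regards to better screening this will eliminate selection bias", and accepts that case detection rate can then no longer be measured as an effect of better screening.

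Two safeguards on blood pressure also bear on the point. During registration, baseline measurements are validated by an external expert blind to arm and to earlier readings (Phases of the trial). The limitations section adds an external blood-pressure doctor who does not know the allocation.

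**The concern.** The protocol answers one specific threat, that unmasked facilities recruit different kinds of patient, with one specific measure: the same screening and diagnosis training in both arms. The sentence that sets out what staff will be trained in does not include that measure for the control arm. If the sentence is followed, the trial gives up case detection rate as a result and does not get the protection it gave it up for.

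The stake is comparability at entry. Eligibility turns on a blood-pressure threshold (systolic above 140 mm Hg, diastolic above 90 mm Hg), and the primary objective is mean change in systolic pressure. If screening is done differently in the two arms, patients near the threshold may be found or classified differently. Randomising the facilities does not correct that, because it happens before the patients are identified.

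**Working it through.** No arithmetic applies. The point is a conflict between statements, and the article gives no figure to recompute. The check sets the passages side by side.

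**1. Is the control training list closed?** Yes. It is limited to three items: registering and reporting, the brochure, and access to two laboratory tests. Neither screening for hypertension nor diagnosing it is among them.

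**2. What do the other sections say about control facilities?**

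| Section | Screening and diagnosis in the control arm |
|---|---|
| Phases of the trial (staff training) | Not in the training list |
| Control arm | Enhanced screening and diagnosis added |
| Recruiting participants | Standardised diagnosis offered |
| Addressing bias, error and limitations | Training equal to the intervention arm |

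The sharpest conflict is between the first row and the last, since both concern training. The wording in Recruiting participants is looser, because the reference to current practice could be read as covering diagnosis as well as care. Setting that row aside, the Control arm and limitations sections still conflict with the training list.

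**3. Would a literal reading create a difference between arms?** The intervention training sentence does not name screening either. But the Rationale says the implementation products, which may include a desk guide and a training module, cover screening and diagnosis. The Interventions section lists enhanced screening and diagnosis among the care dimensions of that arm, and Phases of the trial gives the desk guide to the intervention arm. Read together, and followed literally, these passages train one arm in screening and diagnosis and not the other. This is an inference from several sections, not a single statement.

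**4. Does the order of events allow selection to differ?** Within the first three months of the implementation phase, facilities are shortlisted and randomised, and their staff are then trained according to arm. Patients are registered in the following six months. Outpatients at the facilities are screened (Identifying participants), and the Abstract says the trial is conducted through the facilities' doctors and paramedics. Screening therefore comes after allocation and after arm-specific training.

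**5. Do the external blood-pressure checks close the gap?** In part. They bear on the accuracy of readings in patients already found. They cannot bring in a patient whom screening missed, and the article does not say that a patient whose hypertension is not confirmed externally is removed.

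**6. Does using change from baseline remove the problem?** Only for one component. An offset in technique that is constant within an arm cancels in the change score. A difference in which patients are recruited need not cancel. For example, if entry readings are taken differently, the fall expected from regression to the mean may differ between arms.

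**The case against.** The strongest reply is that this is a loosely worded sentence. Its purpose is to contrast control training with the enhanced case-management training, and the Control arm and limitations sections state the intent clearly. Training modules are separate products, and an article commonly leaves their content to fuller documents. The research team also monitors inclusion and exclusion and maintains the blood-pressure apparatus, and the blinded external checks protect the recorded pressures.

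Much of this stands. It shows that the intended design is probably equal training, and that the primary measurement has some protection. It does not remove the contradiction. The article makes two positive statements about training that cannot both be true, which is different from leaving detail out, and a bias claim depends on one of them.

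A reader might infer more than the text supports:

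- **That control staff will in fact be untrained in blood-pressure measurement.** The sections disagree, so this is unresolved.
- **That exhaled carbon monoxide is measured properly in only one arm.** Training in it is named for neither arm, and the funding statement, "the measurement of hypertension, HbA1c, serum cholesterol and carbon mono oxide in exhaled air will be paid from the project sources", makes no split by arm. The list in Recruiting participants, "access to baseline BP, HbA1c, cholesterol examination will be facilitated, for both arms, through trial resources", omits it for both arms alike. Nothing says that cessation in the control arm rests on self-report.
- **That diabetes and cholesterol status would be determined differently by arm.** Control staff are explicitly trained to access both tests. A research assistant collects laboratory results and checks them against the registration form (Data management procedures).
- **That the bias can be put in mm Hg or in percentage points of cessation.** Any such figure would be pure assumption.

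**Conclusion.** The training sentence is wrong as written. It contradicts the equal screening and diagnosis training in the limitations section and does not fit the Control arm and Recruiting participants sections. Followed literally, it withdraws the safeguard on which the claim to eliminate selection bias depends, and it could make the patients recruited at the entry threshold differ between arms.

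The size and direction of any resulting bias cannot be derived from the document. The risk is lessened, not removed, by the blinded external blood-pressure checks. The conclusion assumes that facility staff carry out the screening, which the article implies, and that the training sentence would be applied as it reads. If the intended training is already equal, the defect lies only in the text, but it should still be corrected because it is the passage that describes what staff are taught.

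**What to change.** Amend the staff-training item in Phases of the trial so that control and intervention staff receive the same training in screening and diagnosis, including blood-pressure measurement for eligibility. State that only training in treatment, education, follow-up and referral differs between arms. The sentence would then agree with the Control arm, Recruiting participants and limitations sections. No endpoint definition needs to change.

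The cost is small, because the Control arm and limitations sections already promise this content. The drawback is that control facilities move slightly further from untouched current practice, which the Control arm section already accepts by adding enhanced screening and diagnosis there.

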**Figure 2 F2:**
[figure not shown]
Phases of the trial.

#### Costing study

A costing analysis will be designed and conducted to inform programmatic decisions by managers and policy makers for possible scaling-up in other districts with ongoing PPM for communicable disease control. The minimal is the incremental cost effectiveness ratio (ICER) analysis of the provider cost (i.e. health department and private facility). The ICER will focus mainly on cost of additional inputs (training, materials, monitoring etc.) at private facility level to achieve the outcomes. This analysis is more relevant for the health department decision makers to consider scaling-up the intervention. The main source of cost data will be records and key informant interviews. We will also explore the possibility of covering, to an extent possible, the patient perspective to the care for HTN and associated conditions. This might involve surveying the registered patients for costing and coping experiences.

#### Explanatory qualitative study

Qualitative interviews with selected care providers (6), and patients (12)^d^ will help to better understand the experiences. A qualified anthropologist, with help of other members, will develop the interview schedules and conduct the semi-structured interviews with various individual categories of interest. The study would collect data on a range of social, economic, service access and quality etc. factors from care providers as well as patients and their families to assess the social and administrative feasibility of said interventions in the programme context and inform refinements before scaling-up to other parts of the country.

#### Dissemination

The results/experiences and products of research will also be shared with wider stakeholders through: a) existing partner networks (e.g. COMDIS,), b) presentations at national and international conferences (e.g. White Ribbon Alliance, World Federation of Public Health Associations), and c) access to resource centers/websites more widely used e.g. WHO.

The scientific papers, based on results of the trial and associated studies, will be submitted to international and national peer-reviewed journals. The potential journals to target includes: BMC cardiovascular disease, Lancet, British Medical Journal, WHO Bulletin, BMC Implementation Science-process evaluation study(s); Health Policy and Planning, Reproductive Health Matters-social science (qualitative studies).

## Discussion

### Current situation

Due to the high burden of disease where 1 in 3 individuals aged above 45 suffers from hypertension, topped with the fact that there is a dearth of a set of available, standardised guidelines for management, the disease is constantly on a hike in Pakistan. The government has made no effort to issue a set of guidelines adapted specifically for our population and this becomes more of a problem when managing CVD in urban population through private practitioners whose practices vary widely. If our set of context sensitive guidelines show an effectiveness in the proposed intervention districts, the 6 facilities in control arm will also be enabled for implementing the enhanced HTN-CVD care guidelines and materials. The enabling primarily will include staff training, guidelines and materials and monitoring support. Consultation with selected provincial health department staff will be conducted for their considering and planning (if possible) the scaling-up of HTN-CVD PPM intervention in other 31 districts of Punjab where PPM for communicable disease (TB) control is already being implemented through GFATM grant.

### Addressing bias, error and limitations

Comparing the socio-demographic and health services profiles of the private facilities does not indicate any significant difference that can potentially lead to differences in care seeking behavior and/or quality of service. The proposed cluster randomization is expected to address the potential selection bias across the two trial arms.

The process of equal screening and diagnosing training in both arms will lead to similar disease intensity patients being recruited in both arms. Although similar training of health professionals in both arms in regards to better screening this will eliminate selection bias, it will lead to a inability to measure ‘case detection rate’ due to better screening.

The lack of masking (blinding) could introduce bias through two routes i.e. “incorrect measurement” and “leakage” from one group to another. There was a possibility of incorrect measurement of “blood pressure outcomes” by the facility doctor, who is aware of the intervention allocation. This possibility of measurement bias will be reduced through an unrelated external BP monitoring doctor who is unaware of the intervention allocation. Contamination across clusters is prevented by keeping a minimum distance between clusters.

The proposed randomization does not allow asking and responding to individual patient preferences. So the trial will not answer the question what would happen if health services are able to offer intervention according to individually tailored patient needs/ convenience. Further work will be needed to test the approaches sensitive to individual preferences, in the local programme setting.

The proposed method of randomization, ie concealed simple randomization has its own limitations. This method does not address the balance of baseline covariates. An alternative approach could have been addresses the need to control and balance the influence of covariates by using stratified randomization. This method can be used to achieve balance among groups in terms of baseline characteristics (covariates) of health facilities based on socio demographics of catchment population they feed into, size of health facility, patient load etc. Different strata /blocks of health facilities may have been made and then simple randomization done in each strata to achieve a balance of covarites. This could have minimized the biased that simple randomization does not address.

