#### Inclusion/exclusion criteria

Among these private facilities ,all newly diagnosed hypertensive (systolic blood pressure >140 mm Hg, diastolic blood pressure >90 mm Hg) male and female patients aged 25 years or more from the catchment population of the respective facility will be included, after an informed consent. The patients to be excluded from the trial are: a) pregnant women, b) persons with advanced chronic disease, c) person with conditions that cause secondary hypertension, d) person with known history of hypertension and/or CVD treatment in the past, e) person not likely to stay in the area for the required follow-up period of 15 months.

Patients who are pregnant and have hypertension will be referred to a gynecologist, patients with advanced chronic disease to a general medical practitioner, and those with a known history of hypertension and/or CVD treatment in the past will be referred to a cardiologist. Only patients who are new cases of hypertension are included in the trial. People with known hypertension are excluded from the trial as they would already be on some sort of antihypertensive drug regimen which may mask the effects of our intervention.

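### Patients are recruited after allocation, apparently by staff who know the arm, so equal screening training cannot be said to eliminate selection bias, and the t-test on SBP change is exposed to any baseline imbalance.

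*Protocol article*

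**What the plan says.** **Order of events.** Under Phases of the trial, the implementation phase opens with three months of set-up, in which "the following arrangements will be made before start registering cases in the trial". In that period the central trial unit "will then randomize the facilities into two trial arms", and facility staff are trained for their own arm. Enrolment comes afterwards: "In the next 06 months of the trial implementation phase, the patients will be registered and enrolled in the trial, as per agreed protocols".

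**Entry of individual patients.** Inclusion/exclusion criteria take in all newly diagnosed hypertensives in the catchment population. Some exclusions need judgement, such as advanced chronic disease or a "person not likely to stay in the area for the required follow-up period of 15 months". Consent is individual: "The patient is recruited only if he/she consents to participate".

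**Claim about bias.** Addressing bias, error and limitations states that "similar training of health professionals in both arms in regards to better screening this will eliminate selection bias". The same section names two routes by which lack of masking could cause bias, mismeasurement and leakage between groups. It also says that the facility doctor knows the allocation.

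**Existing protections.** During enrolment, "the baseline hypertension measurement will be validated by an external expert examination, kept blind to the trial arm". The research team is to monitor inclusions and exclusions closely (Phases of the trial). Item e of Planned statistical tests provides multivariable regression for residual confounding, with stratification by drug class.

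**Analysis.** Item a of Planned statistical tests compares mean SBP change between arms by t-test.

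**The concern.** Randomising facilities makes the facilities comparable in expectation. It does not govern which patients enter within each facility once the arm is known. Staff equally skilled at detecting hypertension can still differ by arm in whom they approach, how they apply the judgement exclusions and who agrees to take part. Training in screening acts on none of these, so the claim of elimination does not follow from its premise.

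The arms could then differ in baseline SBP or prognosis for reasons unrelated to the intervention. A comparison of raw change scores would turn part of a baseline SBP difference into apparent effect through regression to the mean. The trial would also be reported as free of a bias to which its design leaves it open.

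**Working it through.** **1. Sequence.**

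| Step | Timing | Section |
|---|---|---|
| Communal consent | Before randomisation | Ethical considerations |
| Facilities randomised, 6 and 6 | First 3 months | Phases of the trial |
| Staff trained by arm | First 3 months | Phases of the trial |
| Patients consented and enrolled | Next 6 months | Recruiting participants; Phases of the trial |

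No step has individual patients identified or consented before allocation, or by a person blind to the arm.

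**2. Who recruits.** The article does not name the recruiter. That it is facility staff is an inference: the Abstract says the trial is run through facility doctors and paramedics, Data management procedures has them record most of the data, and Phases of the trial trains control staff to register patients.

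**3. The premise of equal training.** Control arm and Addressing bias, error and limitations both give control facilities enhanced screening and diagnosis. The training plan in Phases of the trial limits control-staff training to registering and reporting, the patient brochure and access to tests. Read literally, the training on which the claim rests is not in the training plan.

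**4. What each protection can do.**
- The all-new-cases rule narrows discretion, but remains subject to consent and the judgement exclusions.
- Communal consent does not identify patients.
- Blinded validation checks a measurement. The article does not say that this reading is the analysed baseline.
- Monitoring is aimed at deviations. By itself it cannot show eligible patients who were never approached.
- Regression can adjust only for measured differences. The article names no covariates, and the stratification it describes uses drug class, which is chosen after allocation.

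**5. Illustration of size.** The document gives no figure for this bias, so there is none to reproduce.

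Inputs from Sample size: SD 11 mmHg, ICC 0.02, 6 clusters per arm, 76 patients per cluster, 25% loss. Assumptions: a baseline SBP imbalance of 1 to 3 mmHg, a baseline to follow-up correlation r of 0.3 to 0.7, an imbalance that regresses as ordinary baseline variation does, and a test that respects clustering, with 12 − 2 = 10 df.

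- Analysed per cluster: 76 × 0.75 = 57; per arm 6 × 57 = 342.
- Design effect: 1 + 56 × 0.02 = 2.12.
- SD of change: 11 × √(2(1 − r)), which is 11 at r = 0.5.
- SE at r = 0.5: √(2 × 121 × 2.12 / 342) = 1.225 mmHg.
- Bias of the change score: (1 − r) × imbalance.
- False-positive rate: the probability that a noncentral t with 10 df and noncentrality bias/SE falls outside ±2.228.

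| r | Imbalance (mmHg) | Bias (mmHg) | SE (mmHg) | False-positive rate |
|---|---|---|---|---|
| 0.5 | 1 | 0.5 | 1.225 | 6.6% |
| 0.5 | 2 | 1.0 | 1.225 | 11.5% |
| 0.5 | 3 | 1.5 | 1.225 | 19.9% |
| 0.7 | 3 | 0.9 | 0.949 | 13.8% |
| 0.3 | 3 | 2.1 | 1.449 | 25.9% |

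The SE must move with r because the SD of a change score does.

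**The case against.** The strongest reply is that the plan has several protections. All new cases are to be included, inclusions are monitored, baseline BP is checked by a blinded examiner, and multivariable regression is planned. Its covariate list may reasonably sit in an analysis plan that is not shown. This stands in part: the plan is not unprotected and adjustment is foreseen. But these measures reduce the bias rather than eliminate it, and the t-test on change remains a listed SBP comparison.

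A second reply is that any magnitude is conjecture. This also stands. The imbalance is assumed, and the (1 − r) formula depends on mechanism. If recruiters selected on stable severity, the bias of the change score could be near zero and baseline adjustment could itself mislead.

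A reader might infer more than the text supports in three places:
- **That the article says facility staff judge eligibility and seek consent.** It uses the passive voice, so this is only a reasonable inference.
- **That patients knowingly choose between visibly different packages.** Recruiting participants describes the packages as offered once a patient is recruited, and what patients are told at consent is not shown.
- **That the SBP results will be biased.** The document shows only that they can be.

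**Conclusion.** The statement that selection bias will be eliminated is wrong for this design, and the account of bias from lack of masking omits recruitment after allocation. This rests on the stated order of events, individual consent, the facility doctor's knowledge of the arm, and the inference that facility staff recruit.

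Neither size nor direction can be derived from the document. Under the stated assumptions, an imbalance of 1 to 3 mmHg gives a false-positive rate of about 7% to 20% at r = 0.5. At 3 mmHg the rate is about 14% to 26% over r = 0.7 to 0.3. At r = 0.5 the largest bias shown, 1.5 mmHg, is a quarter of the 6 mmHg target (1.5/6 = 25%). These figures show that a modest imbalance would matter, not that one will arise. The correction should be made because it is cheap and concerns the primary comparison.

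**What to change.** 1. **Wording.** Say that similar screening training may reduce selection bias. State that recruitment follows allocation and may differ by arm. Reconcile the training plan in Phases of the trial with Control arm and Addressing bias, error and limitations on whether control staff are trained in screening.
2. **Primary analysis.** Replace the t-test on change with a cluster-adjusted regression of 15-month SBP on arm, with baseline SBP, age, sex, diabetes and smoking as covariates. Use the blinded external baseline reading where it was taken before treatment started. Do not stratify this comparison by drug class.
3. **Visibility.** Use the existing register and the research assistant's monthly visits to report screened, eligible and consented counts by cluster and arm.

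Entry should not be made conditional on the external reading. That would not touch the judgement exclusions or consent. The article does not place the reading before treatment, so such a condition could add new selection after allocation, and the cost is unknown because the examiner's capacity is not given.

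The cost is a wording change and a small amount of recording and analysis. The limit is that adjustment corrects only for measured differences; the counts reveal differential recruitment but do not prevent it.
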